## Abstract

**Background:**

Chronic heart failure (HF) disease management programs have reported inconsistent results and have not included comorbid depression management or specifically focused on improving patient-reported outcomes. The Patient Centered Disease Management (PCDM) trial was designed to test the effectiveness of collaborative care disease management in improving health status (symptoms, functioning, and quality of life) in patients with HF who reported poor HF-specific health status.

**Methods/design:**

Patients with a HF diagnosis at four VA Medical Centers were identified through population-based sampling. Patients with a Kansas City Cardiomyopathy Questionnaire (KCCQ, a measure of HF-specific health status) score of < 60 (heavy symptom burden and impaired quality of life) were invited to enroll in the PCDM trial. Enrolled patients were randomized to receive usual care or the PCDM intervention, which included: (1) collaborative care management by VA clinicians including a nurse, cardiologist, internist, and psychiatrist, who worked with patients and their primary care providers to provide guideline-concordant care management, (2) home telemonitoring and guided patient self-management support, and (3) screening and treatment for comorbid depression. The primary study outcome is change in overall KCCQ score. Secondary outcomes include depression, medication adherence, guideline-based care, hospitalizations, and mortality.

**Discussion:**

The PCDM trial builds on previous studies of HF disease management by prioritizing patient health status, implementing a collaborative care model of health care delivery, and addressing depression, a key barrier to optimal disease management. The study has been designed as an ‘effectiveness trial’ to support broader implementation in the healthcare system if it is successful.

**Trial registration:**

Unique identifier: NCT00461513

## Background

Despite advances in chronic heart failure (HF) therapies, HF is a leading cause of disability, hospitalization, and death in the United States [1]. Moreover, HF has a major impact on patients’ health status, including their symptom burden (e.g. dyspnea), functional status, and health-related quality of life. However, few HF interventions have specifically targeted these critical patient-centered outcomes. In addition, diminished patient health status is predictive of HF hospitalization, mortality, and resource utilizations, yet health status has not been used to screen for patients to target disease management interventions [2].

While disease management has been variously defined and implemented, some previous studies have reported that HF disease management can reduce rates of hospitalization, and a few have demonstrated reductions in mortality, reductions in cost, or improvements in quality of life. However, many of these studies have been small, single-center trials of short duration, and the association between disease management and improved outcomes has been inconsistent [3-6]. Many HF disease-management studies to date have relied solely on nurse case management rather than multidisciplinary collaborative care, have not leveraged health information technology, and/or have had a limited focus on patient self-care. Most have not included screening and treatment of comorbid depression, or specifically targeted improvement in patient health status as the primary outcome [7]. The Patient-Centered Disease Management (PCDM) trial was designed to address these limitations.

The PCDM trial is evaluating the effectiveness of a collaborative care intervention with telemonitoring and evidence-based HF and depression management in an at-risk population of HF patients with diminished health status. All HF patients from participating centers were identified using existing VA electronic health record databases. The primary outcome of the PCDM trial is 1-year change in patient-reported HF health status, measured using the Kansas City Cardiomyopathy Questionnaire (KCCQ), comparing patients randomized to usual care versus the PCDM intervention. Secondary outcomes include depression, adherence to guideline-based therapies, hospitalizations, and mortality.

## Methods/design

### Study design overview

The primary objective of the PCDM trial is to determine whether a collaborative care HF disease management intervention, including depression assessment and treatment, improves patient-reported health status between baseline and 12 months, as measured by the KCCQ. The study was funded by the United State Department of Veterans Affairs (VA) and conducted in four VA medical centers across the U.S. The VA’s comprehensive electronic medical record was used to identify potential participants for the study. All patients with HF at the four sites were screened with the KCCQ. Eligible patients with diminished heart failure-specific health status (KCCQ summary score <60) were invited to an enrollment visit. Patients provided informed consent, were randomized to the PCDM intervention or usual care, and were followed for a 12-month period. The study was approved by the Institutional Review Boards at each of the study sites.

### Conceptual framework

The conceptual framework for the PCDM intervention highlights HF as a chronic illness often accompanied by co-occurring depression, both of which are prime candidates for disease management approaches, and the importance of health information technology, self-management, and health status outcomes. The Chronic Care Model [8] combines patient self-management support with health system change to achieve productive interactions between a “proactive health care team” and an “activated patient”, producing improved functional and clinical outcomes. The PCDM intervention uses collaborative care as the primary health system change. Collaborative care is the use of multidisciplinary teams to deliver evidence-based treatment to a defined population of patients with chronic illness [9]. The intervention aims to activate patients by promoting self-management of HF and depression through home telemonitoring and education, and when indicated, through integrating depression care into chronic illness care [10]. While telemonitoring in isolation is not effective in improving mortality or hospitalization, [11] telemonitoring might be a useful adjunct to the collaborative care model of health care delivery.

### Setting and population

The study is being conducted at the Denver, Palo Alto, Richmond, and Seattle VA Medical Centers and their affiliated community-based outpatient clinics. All patients with an assigned primary care provider and at least one primary care provider visit during the prior 12 months with a HF diagnosis code in the VA electronic health record were screened for eligibility to participate (see Figure 1 for study population flow).

**Figure 1 F1:**
[figure not shown]
Patient-centered disease management (PCDM) for heart failure trial study population flow.

The study was purposefully designed to target patients with a diagnosis of HF in the VA electronic health record, irrespective of type of heart failure (e.g. with or without preserved left ventricular systolic function). Accordingly, the diagnosis of HF was defined as meeting any one of the following five criteria: (1) A primary inpatient hospital discharge diagnosis of HF (ICD-9 code 428.XX); (2) ≥2 secondary inpatient hospital discharge diagnoses of HF (ICD-9 codes 428.XX) and a primary inpatient hospital discharge diagnosis related to heart disease (ICD-9 codes 410.XX, 412.XX, 413.XX, 414.XX); (3) ≥3 secondary inpatient hospital discharge diagnosis codes related to HF; (4) ≥2 outpatient visit diagnoses of HF, excluding emergency department visits; (5) ≥2 secondary inpatient hospital discharge diagnoses of HF and ≥ 1 outpatient HF diagnosis. This case-finding methodology has been previously described [12]. The primary care provider of each patient was contacted by mail to inform them of the PCDM trial and to allow them to withdraw their patient from further consideration if they deemed the patient to be a poor candidate for study participation.

### Recruitment and study subjects

Following the process of patient identification described above, all remaining patients were mailed a study informational sheet, a decline-to-participate postcard, and a KCCQ questionnaire. Individuals not responding within two weeks received a reminder letter, followed by a phone call if necessary. All returned KCCQ questionnaires were scored, and the individuals scoring < 60 were invited to an enrollment visit if they did not meet any of the exclusion criteria. The exclusion criteria included: (1) cognitive or psychiatric impairment that precludes completion of questionnaires; (2) current residence in a nursing home; (3) irreversible, non-cardiac medical conditions (e.g. metastatic cancer) likely to affect 6-month survival or ability to execute the study protocol; (4) absence of a telephone line in the home; (5) inability to read English; (6) prior heart transplantation; (7) Alcohol Use Disorders Identification Test (AUDIT-C) score ≥ 7 [13].

### Randomization

At the enrollment visit, patients provided informed consent, completed baseline survey measures, and were then randomized. The random allocation sequence was computer generated (SAS version 9.1 procedure PLAN) using a uniform fixed randomization design with an allocation ratio of 1:1 and stratification by site.

### Intervention

#### Collaborative care

The collaborative care team at each site consisted of a local primary care provider, cardiologist, psychiatrist, and nurse coordinator (registered nurse). The team assessed each intervention patient through a review of the VA electronic health record and baseline depression scores from the Patient Health Questionnaire-9 (PHQ-9). The team recommended care changes, as indicated, for a given patient in accordance with the ACC/AHA Guidelines for the Management of Chronic Heart Failure [14] and depression care and telemonitoring data as described below. Collaborative care team recommendations were entered into a progress note in the electronic medical record for review and co-signature by the patient’s primary care provider. Unsigned orders were placed for primary care providers to review and sign at their discretion. This methodology was successfully used within the VA in a study of collaborative care for patients with angina [15].

#### Screening and treatment of depression

Patients were screened for depression at the initial baseline visit using the PHQ-9. Patients who scored ≥ 10 who were randomized to the intervention were entered into the depression care component of the intervention, adapted from a successful collaborative depression care intervention [16]. This included: (1) up to 11 sessions behavioral activation and antidepressant management provided by the nurse coordinator and supervised by the team psychiatrist, with approximately half of visits planned to be by phone and half in person; (2) a depression educational video; (3) depression assessment and self-management education via telemonitoring. The nurse coordinator from each site participated in a two-day training on depression and behavioral activation by the lead study psychiatrist and four weekly follow up calls with the lead psychiatrist. Thereafter, the nurse was supervised by the site psychiatrist with as needed calls with the lead psychiatrist.

#### Telehealth: telemonitoring and patient self-care support

Intervention patients received daily telemonitoring using equipment that has modules for both HF and depression. The system collected blood pressure, pulse, weight, and self-reported symptoms. Patients were asked a pre-programmed series of questions such as, “Are you more short of breath than usual today?”; “Do you have any new or any more swelling than usual in your feet or ankles today?” Patients in the depression care component of the intervention were asked questions about their mood and behavior. Follow-up questions may be generated using branching-chain logic. For instance, a patient responding that he/she is experiencing shortness of breath is then asked to rate the severity. Thresholds are set for notification of the nurse coordinator or for the patient to call the nurse coordinator. The nurse coordinator reviewed the telemonitoring data and could then either provide counseling to the patient or present the patient to the collaborative care team for recommendations.

The self-care programs included medication reminders to promote adherence, education about HF and depression, medication monitoring, and dietary advice. Patients were also taught signs and symptoms to report and ways to manage HF and cardiovascular risk factors such as proper technique and importance of daily self-weighing, adherence to a low sodium diet and medication regimens, and recognition of early signs and symptoms of HF decompensation.

### Usual care

Patients randomized to the usual care arm continued to receive care from their regular medical providers. This care was fully at the discretion of the patient’s regular clinicians, and thus may or may not have included cardiology or mental health clinic care in addition to primary care. Telemonitoring was offered to usual care patients if they were referred for home telemonitoring by any of their providers. However, the telemonitoring data was handled as part of usual care by VA telemonitoring nurses at each facility, rather than being provided to the collaborative care team in the PCDM intervention. At the enrollment visit, patients randomized to the usual care arm were given information sheets that describe self-care for HF and were provided with a scale if needed. Primary care providers were notified if usual care patients screened positive for depressive symptoms based on the initial study surveys. From there, patients’ primary care clinicians assumed responsibility for depression care or referral, at their discretion.

### Outcome measures

The questionnaires and methods used to measure the study outcomes are listed in the Table 1 Baseline measures were collected in person, a research assistant (who was blinded to the randomization arm) collected 3 and 6 month follow-up study outcome measures by phone or in person, and the nurse coordinator collected outcome measures at 12 months.

**Table 1 T1:** Patient-centered disease management (PCDM) for heart failure trial study outcomes

**Domain**	**Measure**	**Timing**			
		**Baseline**	**3-month**	**6-month**	**12-month**

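### The 12-month KCCQ, the primary endpoint, is collected by the intervention team's own nurse coordinator, while the 3- and 6-month scores are collected blind, leaving the primary contrast open to differential response bias of unknown size

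*Protocol article*

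**What the plan says.** The Outcome measures section of the protocol article divides follow-up collection between two roles. For the intermediate visits, "a research assistant (who was blinded to the randomization arm) collected 3 and 6 month follow-up study outcome measures by phone or in person". For the last visit, "the nurse coordinator collected outcome measures at 12 months".

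The last visit is the primary one. The Background states: "The primary outcome of the PCDM trial is 1-year change in patient-reported HF health status". The Study design overview gives the objective as whether the intervention "improves patient-reported health status between baseline and 12 months, as measured by the KCCQ".

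The nurse coordinator has a part in delivering the intervention:

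- The Collaborative care section lists this role as a member of the care team at every site.
- The telehealth section says: "The nurse coordinator reviewed the telemonitoring data and could then either provide counseling to the patient or present the patient to the collaborative care team".
- The depression section adds, for intervention patients with a PHQ-9 score of 10 or more, "up to 11 sessions behavioral activation and antidepressant management provided by the nurse coordinator".
- In the other arm, the Usual care section says that any telemonitoring data were "handled as part of usual care by VA telemonitoring nurses at each facility, rather than being provided to the collaborative care team".

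Table 1 schedules the KCCQ and PHQ-9 at baseline and at 3, 6 and 12 months, and the SCL-20 at baseline and 12 months only. The Limitations section covers contamination, the multimodal intervention and the HF case definition. It does not mention who collects the 12-month data, and no safeguard for that visit is described.

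**The concern.** Stated blinding covers the supporting visits and stops at the visit that decides the trial. This is not a detail left to a fuller document: the article positively names the collector at month 12.

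The KCCQ, PHQ-9 and SCL-20 are patient-reported. A patient who answers to a nurse who has followed their readings, and perhaps counselled them, may answer differently from one who has no such relationship. That relationship is built into one arm only. If it shifts answers in the intervention arm relative to usual care, the shift goes straight into the primary estimate. The PHQ-9 at 12 months is exposed in the same way, and the SCL-20 has no blinded follow-up value at all.

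**Working it through.** **1. Can the nurse coordinator be blind?** The role sits on each site's intervention team, reviews intervention patients' telemonitoring data, may counsel them, and treats those in the depression component. Usual-care telemonitoring data do not go to that team. No separate outcome nurse is described. The nurse coordinator therefore knows who is in the intervention arm.

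**2. What biases the arm comparison, and what does not?** Let δ12 be the true 12-month difference in KCCQ change. Let s_I and s_U be the shifts in reported score caused by nurse collection in the intervention and usual-care arms. Baseline measures were completed before randomization, so they do not enter the argument. Then

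expected observed 12-month difference = δ12 + (s_I − s_U).

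A shift common to both arms (s_I = s_U) cancels. Only the differential part, b = s_I − s_U, biases the result. By the article's account all 12-month data come from the same role, and all 3- and 6-month data from the other. Only the sum δ12 + b is therefore estimable at month 12. The blinded earlier scores enter the likelihood-based model, but do not identify b.

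**3. Inputs (Sample size and statistical power; Randomization).** Meaningful difference 5 points; α = 0.05 (sidedness not stated, two-sided assumed); allocation 1:1. Planned: 600 patients, 30% attrition, SD 18. Updated: 392 patients, attrition below 20% (20% used), SD 15.

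**4. The plan's own power statements.** SE = SD × √(2/n), with n per arm; power ≈ Φ(5/SE − 1.96).

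- Planned: n = 600 × 0.70 / 2 = 210; SE = 18 × √(2/210) = 1.76; power = 81.2%.
- Updated: n = 392 × 0.80 / 2 = 156.8; SE = 15 × √(2/156.8) = 1.69; power = 83.9%.

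Both claims of more than 80% power are reproduced. The point made here does not touch them.

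**5. Illustration of exposure.** In the updated design the smallest significant observed difference is 1.96 × 1.69 ≈ 3.3 points. With no true effect and a differential shift b,

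type I error = 1 − Φ(1.96 − b/SE) + Φ(−1.96 − b/SE).

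The values of b are assumptions; the documents give no bias estimate.

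| b (points) | SD 15, SE 1.69 | SD 18, SE 2.03 |
|---|---|---|
| 0 | 5.0% | 5.0% |
| 1 | 9.1% | 7.8% |
| 2 | 21.9% | 16.6% |
| 3 | 42.5% | 31.4% |

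For b = 2 and SD 15: b/SE = 1.181, so 1 − Φ(0.779) + Φ(−3.141) = 0.2179 + 0.0008 = 0.2187. All three non-zero shifts are below the 5-point meaningful difference.

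**The case against.** The strongest reply is that these are patient questionnaires, not clinician ratings. The KCCQ was mailed to patients at screening, and the article does not say whether the 12-month forms were self-completed or read out. If they were self-completed, the nurse had little direct influence on scoring. This stands as a limit: rater bias is not established. What remains is response bias, because answers handed to a member of one's own care team can still be coloured by that relationship.

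Several stronger readings are tempting, but the documents do not support them:

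- *Every intervention patient reports to their own therapist.* Behavioral activation goes only to those with PHQ-9 of 10 or more. For the others, the nurse's role is telemonitoring review and possible counselling.
- *Usual-care patients report to a stranger.* The article does not say who ran the enrollment visit, so they may have met the nurse there.
- *The bias must favour the intervention.* Social desirability makes that plausible. But intervention patients were also taught which symptoms to report, and fuller disclosure to a familiar nurse would lower their KCCQ scores.
- *The change of assessor alone biases the contrast.* A common assessor effect cancels between arms; only an arm-by-assessor effect matters.
- *A positive result would be uninterpretable.* The blinded 3- and 6-month KCCQ and PHQ-9 give a partial check.
- *Completion at 12 months will differ by arm.* This is possible, but nothing in the article shows it, and the plan already examines missing-data patterns.

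It is also fair to say that enrollment is final, so some 12-month visits may be over. And since patients cannot be blinded in this trial, no choice of collector removes all reporting bias.

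**Conclusion.** The point holds in limited form. The primary 12-month KCCQ is collected by someone who knows which patients are in the intervention arm and takes part in their care, although blinded collection is in place for months 3 and 6. This opens the primary contrast to differential response bias that the mixed model cannot separate from the 12-month treatment effect.

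The documents settle neither size nor direction. The table of error rates shows how sensitive the test is to modest shifts; it is not an estimate of bias. It rests on assumed shifts, two-sided testing at 0.05, 20% attrition, equal arms and a simple two-sample standard error in place of the mixed model's.

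The point is still worth acting on, because it concerns the primary endpoint, modelling cannot repair it, and the avoidable part can be removed with a role the trial already has.

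**What to change.** **Remaining 12-month visits.** Have the existing blinded research assistant collect the KCCQ, PHQ-9 and SCL-20 by the same procedure, by phone or face to face, as at months 3 and 6. Where the nurse must be present, have patients complete the forms themselves and seal them.

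**12-month data already collected.**

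- Record for each patient who collected the data and how the forms were completed.
- Pre-specify the blinded 6-month KCCQ contrast, from the same model, as a supportive sensitivity analysis. It is a different time point: an effect seen at 12 but not 6 months may be a genuine late effect, so this analysis should not serve as a veto.
- Report unblinded 12-month collection as a limitation, and say that the SCL-20 has no blinded follow-up value among visits collected this way.

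**Cost.** Some reallocation of research assistant time, familiarisation with the SCL-20 (not scheduled at months 3 or 6) and one extra analysis. Enrollment and the stated power do not change.

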**Primary Outcome**					
HF-specific Health Status	KCCQ^*^	X	X	X	X
**Secondary Outcomes**					
Depression	PHQ-9^†^	X	X	X	X
	SCL-20^‡^	X			X
Medication Adherence	PDC^§^	X	X	X	X
Guideline-Based Care	Criteria mapping	X			X
Hospitalizations, mortality	Medical Record Review, Self- or Surrogate Report				X

^*^ Kansas City Cardiomyopathy questionnaire.

† Patient health questionnaire-9.

^‡^ Hopkins symptom checklist-20.

^§^ Proportion of days covered.

The primary outcome, HF-specific health status, was measured using the KCCQ. The KCCQ is valid, reliable, sensitive to clinical change, and predicts hospitalization and mortality [2,17,18]. For the secondary outcomes, depression was measured using the PHQ-9 and the Hopkins Symptom Checklist-20 (SCL-20). The PHQ-9 is a valid and reliable instrument that provides a continuous measure of depressive symptoms [19]. The Hopkins Symptom Checklist-20 (SCL-20) is also a valid and reliable measure of depression symptoms [20]. To examine medication adherence, the proportion of days covered (PDC) will be calculated for each patient using established methods, based on the total number of days supplied for filled prescriptions over the observation time interval [21]. Primary medications to be evaluated will be angiotensin converting enzyme inhibitors, angiotensin II receptor blockers, beta-blockers, aldosterone antagonists, statins, digoxin, diuretics, and antidepressants. For a given patient, the proportion of guideline-concordant care will be determined using criteria mapping [15,22]. The guideline-concordant care analysis will be restricted to those patients who have a guideline indication for a medication class, such as beta-blockers for HF with left ventricular systolic dysfunction. Hospitalizations and mortality will be assessed through VA databases, supplemented by patient self-report. Vital status will also be ascertained via the VA Vital Status File which has a sensitivity of 98.3% and specificity of 99.8% compared to the National Death Index [23].

